
### Health professionals

The eligible health providers, physicians, nurses, and multi-professional teams, from HMMD and the PCUs, will be invited to participate as research volunteers. Thus, there is no sample size calculation. The eligible professionals are members of 85 primary care teams from the PCUs (85 physicians, 85 nurses, 12 multi-professional staff members, and 20 PCU managers) and 43 physicians, 73 nurses, 29 multi-professional staff members, and 12 medical residents from the general clinic wards of HMMD, summing to 359 eligible providers in total.

Data on sociodemographic characteristics, educational background, quality of life, burnout, and mindfulness will also be collected. As was described above for patients, or health professionals participating in the study, the Primary Care Attention Tool - Professional Version [21] (only for PCU providers), the World Health Organization Quality of Life (WHOQoL Brief) [22], and the sociodemographic and educational background questionnaires developed by the research team [see Additional file 4] will be administered. The Burnout Clinical Subtypes Questionnaire (BCSQ-12) [31] and the Mindfulness Awareness Attention Scale (MAAS) [32] will also be administered to this group. All questionnaires will be self-administered. Data will also be collected from these professionals on their adherence, participation, and use of acquired knowledge in clinical practice, as well as on their evaluation of the course modules. The sources of these data will be the number of accesses to the knowledge portal for the DLC course and qualitative information from focus groups and the discussion forums.

### Patients’ medical records

To ensure the quality of the data that will be gathered from the medical records, a sub-project will be carried out using the Lean and Six Sigma techniques to improve the quality of the information registered by the health providers. The Lean Six Sigma approach has been used to aggregate value in different processes, reducing waste and adding more uniformity and precision through the application of statistical tools [33, 34]. These principles have been recommended for application in clinical and translational research [35]. This project will be focused on the health records review boards of HMMD and the PCUs, and it will be carried on in partnership with the Process Improvement Department of the HIAE. Requirements for the quality criteria for information in the medical records will be defined and aligned as part of the study, to be audited by the members of these review boards. Additionally, inter-rater reliability analyses will be conducted among the auditors on a regular basis.

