## Background

In structured societies, better care for all must be delivered in a timely and effective manner. Universal health systems face shortages of funding, increasing patient demand, and more complex treatment options [1]. The Brazilian Unified Health System (Sistema Único de Saúde, SUS) aims for the provision of universal access to the population, prioritization of equity in the health services, and integrality across assistance levels [2].

The Regional Healthcare Attention Network (RHAN) is the result of a public policy that has been incorporated in the SUS. RHAN is a framework recommended by the Brazilian Ministry of Health to improve the coordination among the levels of the health care system [3]. The core idea of RHAN is that better communication and the use of evidence-based information by health teams at different points of care should result in coordination and integration in terms of how patients are viewed and managed [4]. Primary care has the most relevant role in RHAN’s coordinating efforts to assess patients who should be referred to the other levels of care (e.g., specialists and hospitals), but patients receiving treatment at other hierarchical levels are also received and managed by the primary care sector [5].

Effective communication among teams based in hospitals and those based in primary care units (PCU) is an essential factor for RHAN functioning regarding patient safety and continuity of care. Hospital discharge summaries have been the main tool used to accomplish these tasks. Frequently, these discharge summaries are incomplete, lacking critical information, and of poor quality. Additionally, they sometimes fail to reach the PCU teams in a timely manner. This lack of communication and information exchange can increase the risk of hospital readmission and lead to discontinuity in patient care [6–9]. Hospitalization rates for ambulatory care sensitive conditions (ACSC) have been inversely correlated with the effectiveness of primary care attention. However, there is currently no consensus on which diseases or conditions should make up the ACSC lists, as these can vary between countries and regions. The Brazilian Ministry of Health developed an ACSC list that includes chronic and infectious diseases [10].

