## Methods/design

### Research setting

Hospital Municipal [name] (HMMD) is a large municipal government-funded general hospital (300 beds) located in the south of São Paulo City (M’Boi Mirim District). The hospital is managed by Hospital Israelita Albert Einstein (HIAE) under a public–private partnership. It is the unique referral hospital for 600,000 people who are registered in 31 PCUs covered by the primary care teams. For the planned study, the 18 PCUs managed by the Center of Studies and Research [name] (CEJAM), a non-government organization that manages the primary care under a public–private partnership framework, will be selected as a convenience sample. Table 1 provides an overview of the study objectives and their associated methods.

**Table 1 Tab1:** Overview of study methods by objective

Element	Objective 1	Objective 2	Objective 3	Objective 4
Objective	To implement and evaluate an Internet-based platform that links health providers at a public hospital to18 primary care units (PCU) to improve communication among health services	To promote and evaluate a distance-learning course (DLC) to update health professionals on the clinical management of ambulatory care sensitive conditions (ACSC)	To verify the impact of the two strategies (communication and course) on patients’ hospital outcomes (30-day readmission rateslength of stay and mortality)	To verify the long-term impact of the two strategies (communication and course) through the follow-up of the patient cohort
Design	Longitudinal study of communications among health services	Cross-sectional study of the course evaluation and longitudinal study of enrolled health care providers	Longitudinal study of patients with ACSC using hospital electronic medical records	Longitudinal cohort study

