Measures	Frequencies of alerts sent by the hospital, answers sent by the PCU, patients’ information being included in the electronic medical record, discharge summaries being sent by the hospital to the PCU Duration of time between each of these steps	DLC: Frequencies of students’ access to didactic materials, participation in forums and face-to-face meetings Professionals: sociodemographic characteristics, quality of life, mindfulness, clinical types of burnout, and primary care attention attributes.	Patients: Main and secondary diagnoses, address, length of stay, discharge type, readmissions, episodes in the emergency department, reference PCU Medical record audits: Content quality of diagnosis, anamnesis, physical exam, lab exams, discharge summary, nurse registers	Patients’ information at inclusion: Sociodemographic characteristics, quality of life, primary care attention attributes. Patients’ information at follow-up: Same as in inclusion, plus PCU medical record information, geographical location of residence, consultations, medications taken, main outcomes (therapeutic plan adherence, disease complications, health services access, mortality, readmission in any hospital) Telemedicine: Reason for telemedicine request, use of diagnosis or treatment information to help with decision making, patients’ obtained outcomes PCU medical record audits: Content quality of registered information
Sample size	Not applicable	All health care providers who accept enrollment in the DLC, of eligible health care providers from the hospital and PCU health teams	All eligible patients during the study period. In total, 3422 patients with at least one ACSC were admitted from 2013 to 2014	560 patients, based on the observed incidence of 16 % readmission within 30 days, fitting a valid logistic model with up to nine covariates. Each interviewer will collect data from at least 10 patients and will be paired with another interviewer to assess inter-rater agreement

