### Study status

At this time, the Internet-based platform has been fully implemented. The DLC was conducted from July 2014 to July 2015. All data related to the health providers have been collected. The Lean Six Sigma project was completed in March 2016. The patients’ selection and inclusion began in November 2014 and was completed in March 2016. Patient follow-up visits are underway. The telemedicine consultations began in April 2016.

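### The Lean Six Sigma record project is a plausible co-intervention on the path to readmission, so a before-after effect cannot be credited to the platform and course alone

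*Protocol article*

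**What the plan says.** The section on patients' medical records states the purpose of the project: "a sub-project will be carried out using the Lean and Six Sigma techniques to improve the quality of the information registered by the health providers". It covers both levels of care: "This project will be focused on the health records review boards of HMMD and the PCUs". Quality criteria for the records are to be defined within the study, "to be audited by the members of these review boards".

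Table 1 lists the hospital record content audited under Objective 3: "Content quality of diagnosis, anamnesis, physical exam, lab exams, discharge summary, nurse registers". The Background describes the starting point, "Frequently, these discharge summaries are incomplete, lacking critical information, and of poor quality", and the consequence, "This lack of communication and information exchange can increase the risk of hospital readmission and lead to discontinuity in patient care".

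Table 1 words Objective 3 as "To verify the impact of the two strategies (communication and course") on hospital outcomes, which include 30-day readmission. Objective 4 names the same two strategies for the long-term follow-up. The Interventions section describes the platform, telemedicine and the course, and does not list the record project.

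On timing, Study status reports: "The Lean Six Sigma project was completed in March 2016". No start date is given.

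**The concern.** A project described as quality assurance for the data would be harmless to the comparison if it only changed how the research team extracts information. This one aims to change what clinicians record, and those records are read by the next clinician. The article's own reasoning runs from poor discharge information to readmission. Better-written records could therefore lower readmission even if the platform and course did nothing.

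There is a second route. Eligible admissions are identified by a recorded main or secondary diagnosis, and diagnosis is one of the audited items. If diagnoses are recorded more fully later on, the set of admissions that counts as ambulatory care sensitive may differ between periods. That bias could run in either direction.

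What is at stake is the conclusion. A health system that adopts only the platform and the course, on the strength of an effect attributed to those two, may not reproduce a result to which the record project contributed.

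**Working it through.** **The plan's own figure.** The sample size of 560 rests on 16% readmission and up to nine covariates. The article does not state the events per covariate. With 10 (assumed), 10 × 9 / 0.16 = 562.5, or 563, which agrees with 560; conversely 560 × 0.16 = 89.6 events, and 89.6 / 9 = 9.96 per covariate. The figure is sound on that assumption, and the present point does not depend on it.

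**The links, side by side.**

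| Link | Where | Stated or inferred |
|---|---|---|
| Project aims to change what providers record, at hospital and primary care units | Patients' medical records | Stated |
| Discharge summary is an audited hospital item | Table 1, Objective 3 measures | Stated |
| Project acts on the discharge summary | The two rows above, combined | Inferred |
| Poor discharge information can raise readmission risk | Background | Stated |
| Effect worded as that of two strategies | Table 1, Objectives 3 and 4 | Stated |
| Historical controls; no concurrent control described | Sample and study design | Stated |

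**The dates.**

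- Objective 3 admissions: 2013 to 2017
- Course: July 2014 to July 2015
- Cohort inclusion: November 2014 to March 2016
- Record project: start not given, completed March 2016
- Telemedicine consultations: from April 2016
- Platform: fully implemented at the time of writing, no start date given

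Two things follow. For Objective 3, the project ended inside the window, so admissions after March 2016 come after its completion and an unknown number of earlier ones fell during it. For the cohort, inclusion closed in the month the project ended. The 30-day outcome of the last patients included falls at about April 2016, so exposure of the cohort's 30-day readmission depends almost wholly on the missing start date. The one-year follow-up of patients discharged after March 2015 does run past completion.

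**How small a shift would matter (illustration only).** Suppose the two strategies have no effect and the record project alone moves readmission from 16% to p₂. Take n₁ = 3422 baseline patients (the 2013–2014 count in Table 1) and a later period of n₂ patients, with a two-sided 5% test of two proportions. The article gives the 5% level but not the sidedness, and under Objective 3 it names models only for length of stay and mortality, so this test is a simplification.

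Power ≈ Φ[(|p₁ − p₂| − 1.96·SE₀) / SE₁], where SE₀ = √[p̄(1 − p̄)(1/n₁ + 1/n₂)] with p̄ the pooled proportion, and SE₁ = √[p₁(1 − p₁)/n₁ + p₂(1 − p₂)/n₂].

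For p₂ = 0.15 and n₂ = 3422: SE₀ ≈ SE₁ ≈ 0.00875, so the argument is (0.010 − 0.01715) / 0.00875 = −0.82 and the power is 21%.

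| p₂ (assumed) | n₂ = 3422 (assumed) | n₂ = 1711 (assumed) |
|---|---|---|
| 15% | 21% | 15% |
| 14% | 64% | 47% |
| 13% | 94% | 82% |

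These are the chances of a significant before-after difference that owes nothing to the two strategies. Neither the shifts nor the later sample sizes are document figures.

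**The case against.** Five arguments can be made on the other side.

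1. *The discharge summary is never named as a target of the project.* This is correct. A reader might infer that the project upgraded discharge summaries, or that it reached every patient at the hospital. The article says neither, and shows no improvement in them. What stands is plausibility: a general aim of improving recorded information, together with an audit list that contains the discharge summary.

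2. *Exposure of the main cohort may be small.* It is tempting to count the months after March 2016 as the exposed share of a post-intervention period. The article defines no such period, and no cohort patient was included after that month. Table 1 also places the modelling of readmission under Objective 4, the cohort. Exposure therefore cannot be sized, but it cannot be taken as nil either, since the project was running for some unknown time before March 2016.

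3. *Record content and the communication strategy overlap.* The platform carries the discharge summary to the primary care unit, so content and delivery are partly one mechanism. This is fair, and it is a reason to speak of a package rather than to treat the project as a wholly separate rival cause.

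4. *The article already concedes the limits.* The Discussion admits difficulty in isolating the effects of the proposed interventions and mentions data quality as a theme under study, and Table 1 plans comparisons of record adequacy over time. These help with interpretation. They do not identify the record project as a possible cause of changed readmission, and the objectives still name two strategies.

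5. *A model term is a detail for the full protocol or analysis plan.* Agreed, and its absence is not the point here. The point is that two things the article does state do not fit together: a project that changes recording practice, and an effect worded for two other components.

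**Conclusion.** The concern holds as one of attribution. With historical controls and no concurrent control described, an effect worded as that of the platform and course cannot be separated from that of the record project, whose stated aim lies on the study's own path to readmission and whose completion falls inside the Objective 3 window.

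Its size is not known. The document supports neither a share of patients exposed nor an effect of the project. The illustration shows only that an assumed fall of two or three percentage points from this source could often produce a significant result in a comparison of the assumed size, while a one-point fall usually would not. The bias through recorded diagnoses has no known direction.

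The conclusion rests on the inferred link to the discharge summary and on the absence of any described concurrent comparison. A reader might also infer that a time step at March 2016 would isolate the project. It would not: telemedicine consultations began the next month and the project's start is unknown. The sample size is unaffected.

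**What to change.** - Name the record project as a co-intervention in Objectives 3 and 4.
- Word the conclusions on readmission and the other patient outcomes as the effect of the whole package, not of the platform and course alone.
- Report the project's start and completion dates alongside those of the platform, course and telemedicine, so that readers can see which admissions each could have reached.
- If the Objective 3 series is shown with a step or split at March 2016, label it descriptive only. The periods are too close together to separate the components.

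The cost is a few sentences and one table of dates. No data collection or sample size changes. The downside is a less specific claim: the study could no longer state an effect of the two strategies by themselves, which this design does not allow it to isolate in any case.

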
### Sample and study design for impact evaluation

PatientsThe impact evaluation of the integration strategy will use a quasi-experimental cohort with historical controls design. Participants will be adult patients hospitalized for ACSC who will be followed up 1 year after their hospital discharge. Patients’ data will be compared with data on the same patients from different time periods as historical controls, using medical records dating at least 1 year before and 1 year after the patients’ inclusion in the study.The sample of patients will be selected in two stages. First, a convenience sample of 18 PCUs will be selected, as described above. In the second stage, 560 hospitalized adult patients living in the territories covered by and registered in the selected PCUs will be selected based upon their main or secondary diagnosis, which must fit the Brazilian ACSC criteria, excluding female pelvic disorders and pregnancy-related diseases (Table 2). The calculation of this sample size was based on the 2013–2014 HMMD incidence of 30-day readmissions for ACSC, which was 16 %. This sample size will permit a valid logistic model with up to nine covariates to be fit [20].

**Table 2 Tab2:** Diagnoses included in this study and their International Classification of Diseases (ICD-10) codes

Diagnosis	ICD-10 code
Infectious gastroenteritis and complications	E86, A00–A09
Gastrointestinal ulcer	K25–K28, K92.0, K92.1, K92.2
Ear, nose, and throat infections	H66, J00–J03, J06, J31
Bacterial pneumonias	J13–J14, J15.3–J15.4, J15.8–J15.9, J18.1
Diseases of the lower airways	J20, J21, J40–J44, J47
Asthma	J45–J46
Tuberculosis	A15.4–A15.9, A16.3–A16.9, A17.1–A17.9
Pulmonary tuberculosis	A15.0–A15.3, A16.0–A16.2
Heart failure	I50, J81
Hypertension	I10–I11
Angina pectoris	I20, I24
Cerebrovascular diseases	I63–I67, I69, G45–G46
Diabetes mellitus	E10–E14
Infection in the kidney and urinary tract	N10–N12, N30, N34, N39.0
Epilepsies	G40–G41
Syphilis	A51–A53

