Infection of the skin and subcutaneous tissue	L01, L02, L03, L04Exclusion criteria are being under palliative care or dying during the first hospitalization, as well as being unable to respond to the questionnaires because of a cognitive deficit or an unstable clinical condition. The data of all eligible ACSC patients identified by the research team will be analyzed according to their diagnosis, length of stay, outcomes (discharge, death, or transfer to another hospital), and readmission rates.The Brazilian validated version of the Primary Care Attention Tool [21], the World Health Organization Quality of Life (WHOQoL Brief) [22], and a sociodemographic questionnaire [see Additional file 2] developed by the research team based on other validated instruments [23–27] to collect data on social and environmental characteristics will all be administered at the bedside after the patient has signed the informed consent form, and again at the follow-up visit in the patient’s home or PCU, as chosen by the patient. At the follow-up, an additional questionnaire about treatment plan adherence [see Additional file 3], disease monitoring, and access to all levels of the health services will also be administered.Data on the selected patients will be gathered from their medical records and the electronic system of the São Paulo Municipality (SIGA SAÚDE), which registers all patient visits to the points of care managed by the São Paulo municipal health system, as well as prescribed medications. From both HMMD and the PCUs, medical record data will be collected covering the time period at least 1 year before and 1 year after hospitalization, following the historical control design chosen for this study, to search for evidence related to the number of consultations, health promotion and education actions, and access to the other levels of the SUS. Several telemedicine-related variables will also be collected: the reason for the consultation, diagnostic or therapeutic aid, information use in decision making, and patient’s obtained outcomes. All data collected by the research team will be submitted to an inter-rater reliability analysis using Gwet’s coefficient [28].At the follow-up visit, some interviews will be video recorded, for patients who authorize the use of their images, to obtain additional information that will be analyzed qualitatively about their use, personal impressions, and satisfaction with the health system. All interviews will be transcribed and coded through subsequent qualitative analysis, informed by the discourse of the collective subject theory [29]. All of the participating patients’ addresses will be mapped using the free software and open data service Open Street Map [30] assess correlations between social and environmental vulnerabilities and patient’s health status.

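### The study's own record-improvement project may raise chart-counted before/after measures through fuller recording, with no change in care

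*Protocol article*

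**What the plan says.** The section Patients' medical records describes a sub-project "using the Lean and Six Sigma techniques to improve the quality of the information registered by the health providers". It presents this as a way to secure data quality. Its scope is both sites of care: "This project will be focused on the health records review boards of HMMD and the PCUs". Study status gives the timing: "The Lean Six Sigma project was completed in March 2016". No start date is stated. The same section says of recruitment: "The patients’ selection and inclusion began in November 2014 and was completed in March 2016".

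Sample and study design for impact evaluation sets the comparison: "Patients’ data will be compared with data on the same patients from different time periods as historical controls". For the hospital and the primary care units, "medical record data will be collected covering the time period at least 1 year before and 1 year after hospitalization", and one stated purpose is "to search for evidence related to the number of consultations, health promotion and education actions", together with access to other levels of the public system. That section also names SIGA SAÚDE as a data source that registers visits to municipally managed points of care and prescribed medications.

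Table 1 (Objective 4) describes the primary care unit records as paper-based. Under Objective 3 it plans audits of record adequacy, compared over time with chi-square tests. The Data analysis plan compares results over time with generalized linear models and generalized estimating equations. The Discussion concedes in general terms that the interventions' effects will be hard to isolate, but does not mention recording.

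**The concern.** The sub-project can improve only what is written once it is under way. It cannot repair entries already made in the look-back year. Each patient's after-window is later than that patient's before-window, so any gain in recording falls mainly on the after side. In a paper chart, an activity that was not written down is not counted. A higher count afterwards can therefore mean more care, more complete notes, or both.

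No concurrent group shares the change in recording, so a period term in the planned models estimates the sum of the two. For chart-counted items, a positive result could not be attributed to the communication platform and the course. It might reflect only the study's own effort to improve the notes. The article presents the sub-project as a safeguard and does not recognise this consequence.

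**Working it through.** **The plan's own figures.** The article gives no figure for record completeness, so there is nothing to reproduce on that point. The cohort size of 560 is not in dispute: assuming ten events per covariate, 10 × 9 / 0.16 = 562.5.

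**Inputs from the article.** Inclusion ran from November 2014 to March 2016, which is months 0 to 16. The sub-project was completed in March 2016 (month 16). Each patient has one year before and one year after hospitalization.

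**Assumptions, not in the article.** Inclusion is uniform over months 0 to 16. True care is constant. Recorded count = true count × completeness. Completeness is 70% at first and 85% or 75% later.

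**Step 1: share of window time after completion.** A patient included at month t has an after-window from t to t + 12.
- For t below 4, none of it lies after month 16.
- For t from 4 to 16, the share is (t − 4)/12.
- The average over inclusion is (1/16) × ∫ from 4 to 16 of (t − 4)/12 dt = (1/16) × 144/24 = 0.375.
- No before-window extends past month 16, so that share is 0.

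**Step 2: apparent rise, step change at completion.** Ratio = (c0 + 0.375 × (c1 − c0)) / c0.
- 70% to 85%: (0.70 + 0.05625)/0.70 = 1.080, or about +8.0%.
- 70% to 75%: (0.70 + 0.01875)/0.70 = 1.027, or about +2.7%.

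**Step 3: gradual improvement up to March 2016.** The sub-project's start is unknown, so it was varied from July 2014 to November 2015. The average fraction of the full gain reached is then:
- start July 2014: 0.825 in after-windows, 0.322 in before-windows;
- start March 2015: 0.712 and 0.126;
- start November 2015: 0.500 and 0.014.

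For 70% to 85% the ratios are 0.8238/0.7483 = 1.101, 0.8068/0.7189 = 1.122 and 0.7750/0.7021 = 1.104. The rise is about 10% to 12%.

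**Step 4: upper bound.** If every before-window preceded the gain and every after-window followed it, the ratios would be 0.85/0.70 = 1.214 (+21%) and 0.75/0.70 = 1.071 (+7%). The study calendar does not separate the periods in this way.

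**Step 5: could a rise of this size reach significance?** Take 560 patients, an assumed 4 true contacts a year, Poisson counts and the step change from 70% to 85%.
- Recorded means are 4 × 0.70 = 2.8 and 4 × 0.75625 = 3.025.
- Standard error = √((2.8 + 3.025)/560) = 0.102, so the expected z is 0.225/0.102 = 2.21.
- The chance of a significant rise at two-sided 5% is Φ(2.21 − 1.96), about 0.60.
- If the variance is twice the mean, z is 1.56 and the chance is about 0.34.

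With no change in recording, the chance of a significant rise would be 0.025.

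**The case against.** **The article already has partial protection.** SIGA SAÚDE is a planned source for visits and prescriptions, record adequacy is audited over time, and the Discussion concedes limits on attribution. This is fair, and it narrows the point. It does not remove it. The article does not make SIGA the source for the counts, and it looks for consultations in the hospital and unit records. Auditing adequacy can show that recording changed but does not correct the counts. The general limitation does not name this mechanism. The additional questionnaire on access is given only at follow-up, so it has no earlier value to compare with.

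**The sub-project may have had little effect.** The article gives its aim and completion date, but not its result. This stands: chart-counted items may rise, and it cannot be said that they will.

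**Source ranking is analysis-plan detail.** A condensed article may leave such detail out. The point here is different: the design as described changes the measuring instrument during a before/after comparison.

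**A stronger reading that the article does not support.** A reader might infer that fuller coding of secondary diagnoses changes the case mix and so biases the readmission rate. The phrase "main or secondary diagnosis" describes selection of the 560-patient cohort. There the controls are the same patients, and inclusion ended in the month the sub-project was completed. For Objective 3, Table 1 requires only at least one ambulatory care sensitive condition. It lists main and secondary diagnoses as measures, so such a shift is conceivable, but nothing says the sub-project increased the coding of secondary diagnoses. The direction is also open. Suppose 15% more patients entered on a base rate of 16%. With a 10% readmission rate among them the result is (0.16 + 0.15 × 0.10)/1.15 = 15.2%; with 20% it is (0.16 + 0.15 × 0.20)/1.15 = 16.5%. All of these added values are assumptions.

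**Conclusion.** The concern holds for items counted from chart entries: health-promotion and education activity, and consultations and access where these are taken from the charts. For these, the before/after contrast mixes fuller recording with better care, and the planned models cannot separate the two. Any bias from improved recording is upward.

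Its size is unknown. For completeness rising from 70% to 85%, the false rise is about 8% with a step at completion and 10% to 12% with gradual improvement. For 70% to 75% with a step it is about 2.7%. The +21% and +7% are limits that apply only to fully separated periods. All of these figures rest on assumed completeness values and constant care; the calendar-based ones also assume uniform inclusion.

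Readmission, length of stay and mortality are admission and discharge events and are not shown to be affected. It would be wrong to conclude from this point that the primary outcome is biased.

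**What to change.** For the before/after comparisons:

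1. Make SIGA SAÚDE the primary source for visit and prescription counts in both periods, with chart counts as secondary. This assumes that the sub-project, which targeted the hospital and unit records, did not also change entry into SIGA; the report should say so.
2. Report items available only from charts, such as health-promotion and education activity, as process or recording results and not as impact of the interventions.
3. State the sub-project's start and end dates, so that the overlap with each patient's windows can be seen.
4. Show the audit adequacy results by period beside the chart-based changes, where such results exist. The article does not show that scores exist for the look-back year or by unit, so an adjusted model should not depend on them.

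The cost is mainly wording of the analysis. Follow-up was still under way when the article was written, and SIGA was already a planned source. There are two downsides: SIGA covers only municipally managed points of care, and fewer outcomes can be claimed as impact. Restricting the Objective 3 cohort to main diagnoses is not needed for this point and would give up patients.
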